23. Deployment Risk and Resiliency Inventory-2 (DRRI-2) Post-Deployment Social Support subscale: The DRRI-2 (Vogt et al., 2012) is a suite of 17 individual scales that assess key deployment-related risk and resilience factors with demonstrated implications for veterans' long-term health. The Post-Deployment Social Support subscale will be used to assess post-deployment social support as a factor that may affect recovery.
24. Patient Health Questionnaire-15 (PHQ-15) (Kroenke, Spitzer, & Williams, 2002). The PHQ-15 is a brief, self-administered

*Project Remission: Maximizing Outcomes with Intensive Treatments for Combat-Related PTSD*

- questionnaire that assesses somatic symptom severity. Participants rate the severity of 15 somatic symptoms as 0 (not bothered at all), 1 (bothered a little) or 2 (bothered a lot). The scale has strong psychometric properties in terms of internal reliability, convergent validity, and discriminant validity (Kroenke, et al., 2002), and has been used in recent research using an active duty military sample (Hoge, et al., 2008).
25. Trauma Related Guilt Inventory (TRGI) (brief): The TRGI was developed to assess guilt feelings and attitudes about a specific traumatic event (Kubany, Haynes, Abueg, Manke, Brennan, Stahura, 1996). Often survivors of trauma experience guilt related to the trauma about things they did or did not do or feelings they had or did not have. A combat veteran may experience guilt about having provided first aid to some of his or her wounded colleagues but not others even though it was not possible to care for everyone. Or, an individual may experience survivor's guilt not understanding why he lived while others died. These feelings of guilt can be important in evaluating the various treatments for PTSD. The TRGI is scored into three scales (i. e., 4-item Global Guilt Scale, 6-item Distress Scale, and a 22-item Guilt Cognitions Scale) and 3 subscales (i. e., the Hindsight-Bias / Responsibility Subscale, the Wrongdoing Subscale, and the Lack of Justification Subscale). Psychometric testing has been conducted using almost 600 individuals including 357 university students, 163 women receiving counseling services in a battered women's program, and 74 Vietnam veterans. Internal consistency was high across all the testing samples. In the sample of Vietnam veterans the alpha coefficient ranged from 0.66 to 0.94. In the Vietnam veterans, the scores on the various scales and subscales were significantly correlated with the Posttraumatic Checklist – Military (PCL-M), the Mississippi Scale for Combat-Related Posttraumatic Stress Disorder, the Zung Self-Rating Depression Scale, the Guilt Inventory, and the Social Avoidance and Distress Scale with reliability coefficients ranging from 0.36 to 0.77 ( $p < .05$ ). In a sample of 32 university students, the test-retest correlations after two days ranged from 0.74 to 0.83. An abbreviated 16-item version of the TRGI will be used in the STRONG STAR studies allowing only for the calculation of the three subscale scores. The Hindsight-Bias / Responsibility Subscale score = (sum of scores on Items 1, 5, 9, 14, 19, 23, and 26) divided by 7. The Wrongdoing Subscale score = (sum of scores on Items 3, 7, 11, 16, and 21) divided by 5. And, the Lack of Justification Subscale score = [sum of scores on Items 4 (R), 8 (R), 12 (R), and 17 (R)] divided by 4.
26. Posttraumatic Cognitions Inventory (PTCI): The PTCI is a 36-item questionnaire that was developed to determine how an individual views the trauma and its sequelae in an attempt to understand both how PTSD develops and is maintained (Foa, Elhers, Clark, Tolin, & Orsillo, 1999). Using an emotional processing theory, Foa and her colleagues (1999) have suggested that PTSD is a consequence of disruptions in the normal processes of recovery when an individual has excessively rigid concepts about self and world rendering the person vulnerable if a traumatic event occurs. Thus the PTCI was developed as a measure of trauma-related thoughts and beliefs. It is comprised of three subscales (Negative Cognitions about the Self, Negative Cognitions about the World, and Self-Blame). The measure was tested in almost 600 adult volunteers recruited from two university PTSD treatment clinics as well as a university community. Approximately 65% ( $n=392$ ) of individuals reported having experienced a trauma in which their own life or that of another person was perceived to be in danger and their response at the time included intense terror, horror, or helplessness (Criterion A event). The remaining 35% ( $n=162$ ) denied such a traumatic experience. Of those who had experienced a trauma, 170 had PTSD symptoms of at least moderate severity while the remaining 185 reported a low symptom severity. The three subscales of the PTCI demonstrated internal consistency with alpha coefficients ranging from 0.86 to 0.97. Convergent validity was demonstrated comparing the PTCI to appropriate subscales of the World Assumptions Scale and Personal Beliefs and Reactions Scale. Significant correlations between the appropriate subscales ranged from 0.20 to 0.85. The PTCI was able to differentiate individuals with and without PTSD demonstrating discriminant validity (sensitivity = 0.78, specificity = 0.93). Test-retest reliability for each of the three subscales at a 1-week interval ranged from 0.75 to 0.89 and for a 3-week interval ranged from 0.80 to 0.86.
27. Childhood Trauma Questionnaire (CTQ): (Bernstein and Fink 1998) The CTQ is 28-item self-report screening for childhood trauma. This measure is included because childhood trauma history has been found to influence neuroendocrine and neurosteroid function beyond what is explained by PTSD (Van Voorhees, Dennis et al. 2014). The CTQ has good convergent validity, internal consistency (.66-.92) and test-retest reliability (.79 -.86) (Bernstein and Fink 1998).
28. Insomnia Severity Index (ISI). The ISI (Morin, 1993) is a 7-item self-report measure that assesses perceived severity of insomnia. Each item uses a 4-point Likert type scale from 0 (not at all satisfied) to 4 (very much satisfied). The items sum to produce a total score (range 0 – 28). The ISI has an internal consistency alpha coefficient of 0.74, and has shown convergent validity with other measures such as the Pittsburgh Sleep Quality Index ( $r = 0.67$ ), the Dysfunctional Beliefs and Attitudes about Sleep ( $r = 0.55$ ), and sleep diaries ( $r$  ranges from 0.32-0.91) (Bastien, Vallieres & Morin, 2001).

29. PROMIS Sexual Function and Satisfaction Measures: The PROMIS questionnaires are a system of reliable measures of patient-reported health status for physical, mental, and social well-being developed with funding under the National Institutes of Health (NIH) Roadmap for Medical Research Initiative to re-engineer the clinical research enterprise (<http://www.nihroadmap.nih.gov>). PROMIS measures can be administered across a wide variety of chronic diseases and conditions and in the general population (Cella et al, 2010). One of the PROMIS instruments is a Sexual Functioning Inventory (Jeffery et al, 2009), a revised version of which was recently published (PROMIS Sexual Function and Satisfaction Measures version 2.0; Weinfurt et al., 2015). The PROMIS Sexual Function and Satisfaction Measures (Weinfurt et al., 2015) provide scores on 11 different sub-domains of sexual function: interest in sexual activity, lubrication (female only), vaginal discomfort (female only), clitoral discomfort (female only), labial discomfort (female only), erectile function (male only), orgasm ability, orgasm pleasure, oral dryness, oral discomfort, satisfaction. Each question asks respondents to report on their experiences over the past 30 days. All sub-domain scores are expressed as T scores (mean = 50, standard deviation = 10). In testing with a nationally representative sample of 3516 U.S. adults, correlations between the PROMIS Sexual Function and Satisfaction Measures and corresponding sub-domains of two well-established measures, the Female Sexual Function Index (FSFI) and the International Index of Erectile Function (IIEF), ranged between .67 and .94. The sub-domains of the instrument discriminate between people who had and had not asked a provider about sexual problems. Test-retest correlations over one month are >.65 for all sub-domains ("Sexual Function and Satisfaction Measures User Manual," 2012).
30. PROMIS Sleep Disturbance and Sleep-Related Impairment short forms: The PROMIS Sleep Disturbance and Sleep-Related Impairment short forms (Yu, Buysse, & Germain, 2012) are self-report measures of past-week sleep disturbance and past-week sleep-related impairment, respectively, derived from the larger PROMIS item banks (Buysse et al., 2010). Each short-form measure includes 8 items, with most items (symptoms) scored in intensity from 1 ("not at all") to 5 ("very much"). Each measure has shown strong reliability and construct validity (Yu et al., 2012).
31. Snoring, Tired, Observed, Blood Pressure (STOP) Sleep Apnea Screen: To better understand sleep disturbance associated with PTSD and PTSD treatment, the STOP screen (Chung et al., 2008) will be administered to screen for sleep apnea. The STOP is a four-item questionnaire developed and validated in 211 pre-operative surgical patients. Based on the endorsement of 2 or more questions, the sensitivity of the STOP ranged from 66% to 80% as compared with the apnea-hypopnea index (AHI) of polysomnography depending upon the AHI cut-off used. Individuals answering "yes" to 2 or more of the questions will be advised that they may be at risk for having sleep apnea and advised that they may want to speak with their primary care provider to consider referral for an overnight sleep evaluation.
32. Fagerstrom Test for Nicotine Dependence (FTND): The FTND (Heatherton et al., 1991) is a 6-item self-report measure that assesses severity of nicotine dependence. Questions probe both quantity of nicotine use (e.g., number of cigarettes per day) and pattern of use (e.g., time to first cigarette in morning). Respondents choose among response options, each of which is assigned a numerical value, with higher numbers corresponding to greater nicotine dependence. Scores on all items are summed to create a severity index (0-2 = very low dependence; 3-4 = low dependence; 5 = medium dependence; 6-7 = high dependence; 8-10 = very high dependence). The Fagerstrom scale has been shown to have high convergent validity with biochemical indices of nicotine use, and the measure has shown acceptable internal consistency (Heatherton et al., 1991). A review of 26 studies of the psychometric characteristics of the Fagerstrom found that it is a reliable instrument for measuring nicotine dependence in diverse settings and populations (Meneses-Gaya et al., 2009).
33. Fagerstrom Test for Nicotine Dependence – Smokeless Tobacco (FTND-ST): This is a modified version of the Fagerstrom Test that focuses on smokeless tobacco use, whereas the original Fagerstrom focuses exclusively on smoking. Like the FTND, the FTND-ST is a 6-item self-report measure of severity of nicotine dependence that has demonstrated convergent validity with biochemical indices of nicotine use (Ebbert et al., 2006; Ferketich et al., 2007). As on the original FTND, respondents choose among response options, each of which is assigned a numerical value, with higher numbers corresponding to greater nicotine dependence. Scores on all items are summed to create a severity index (range = 0–10).
34. Credibility/ Expectancy Questionnaire (CEQ): The CEQ is a 6-item measure that was designed to assess treatment expectancy and rationale credibility for use in clinical outcomes studies (Devilly & Borkovec, 2000). It has been expanded from a 5-item measure designed primarily to assess credibility (Borkovec & Nau, 1972), 4-items of which have been used by both Foa and Resick ([name], personal communication, February 22, 2010; [name], personal communication, February 23, 2010; [name], personal communication, February 25, 2010) with the name Expectancy of Therapeutic Outcomes (ETO). The 6-item CEQ assesses both whether the person cognitively understands how the therapy works (credibility) as well as whether the person affectively believes that the therapy will work for them personally (expectancy). The 6-item CEQ has been tested in 217 individuals including 68 male Vietnam veterans and 58 female

*Project Remission: Maximizing Outcomes with Intensive Treatments for Combat-Related PTSD*

spouses, 69 individuals diagnosed with general anxiety disorder who had received treatment, and 22 individuals who had received either Cognitive Based Therapy (CBT) or Eye Movement Desensitization and Reprocessing (EMDR) for the treatment of PTSD. The scale demonstrated high internal consistency (alpha coefficients ranged from 0.84 to 0.85). Test-retest reliability over a one-week period was found to be 0.82 for expectancy and 0.75 for credibility. The CEQ was able to differentiate between two treatment rationales in one study, one with and one without an encompassing theory while maintaining equivalence between three rationales in another study. Responses to four questions are scored using a 9-point Likert scale (1= not at all, 9= extremely). Responses to two of the questions are scored using an 11-point Likert Scale (0% to 100%). The combined responses are used to generate a score for credibility and another score for expectancy.

35. The Independent Evaluator Blind Form measures the independent evaluator's best guess about the study treatment that the subject received, level of confidence in this guess, and how unblinding could potentially have occurred. This form will be used at treatment completion and follow-up for all CAP psychotherapy RCTs that include independent evaluation of outcomes.

36. Genetic Biomarkers. Four tubes of blood will be collected and processed for DNA, RNA, plasma, and serum processing.

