| 6. Combat-Related PTSD Beliefs Inventory                                                                 | X         |         |                 |                   |                   |                   |         |         |         |
| 7. History of Head Injuries                                                                              | X         |         |                 |                   |                   |                   | X       | X       | X       |
| 8. Health Questionnaire                                                                                  | X         |         |                 |                   |                   |                   | X       | X       | X       |
| 9. MINI -7.0 (Mini International Neuropsychiatric Interview for DSM-5) Psychosis and Mania modules only. | X         |         |                 |                   |                   |                   |         |         |         |
| 10. Alcohol Use Disorders Identification Test (AUDIT)                                                    | X         |         |                 |                   |                   |                   |         |         |         |
| 11. Deployment Risk and Resilience Inventory (DRRI-2) Subscales:                                         | X         |         |                 |                   |                   |                   |         |         |         |

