## 7.4 Statistical Consideration

**7.4.1 Sample Size Estimation.** The primary hypotheses are tests of treatment differences in pre-post means using the pre-treatment score as a covariate. Statistical power for the analysis of covariance with  $r = .50$  between baseline and post-treatment is .81 to detect a standardized mean difference of .35. An analysis of unadjusted pre-post difference scores with  $N = 100$  per group would have power = .80 for a standardized difference of about  $d = .40$ . Cohen (1988) defined  $d = .2$  as “small,” and  $d = .5$  as “medium.” The PCL-5 in our experience has a baseline standard deviation of about 15, and smaller differences than  $d = .35$  are unlikely to be clinically meaningful. For differences in diagnostic proportions (Hypothesis 2),  $N = 100$  gives power = .80 for a difference of about 20% (i.e., 45% vs. 65% or 50% vs. 70%). This is an odds ratio of about 2.3, roughly equivalent to Cohen’s  $d = .45$ . For bivariate correlations,  $N = 100$  has power = .88 to detect a medium  $r = .30$ .

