### 7.4.3 Data analysis.

**7.4.3.1 General Statistical Considerations.**

Data will be entered into the STRONG STAR database on a secure UTHSCSA server meeting HIPAA requirements on an ongoing basis using specialized software that provides for double entry and numerous internal validity checks and produces regular reports on data flow to identify any ongoing recruitment issues. Prior to statistical analyses, data will be inspected for outliers, unusual distributions that suggest transformations such as log, and patterns of missing data. Data will be analyzed using the SAS statistical system (SAS 9.4).

Missing Data. An Intent-to-treat analysis will be used with a likelihood-based analysis method which is robust if data are missing at random. Outcome data will be collected on all participants randomized, even if they elect to end treatment or study participation. If a reasonable predictive model for missing data can be found and patterns of attrition suggest possible bias, the primary analyses will be supplemented with inverse propensity score weighting and multiple imputation (Hirano et al., 2003, Lunceford & Davidian, 2004). This approach will make it possible to perform sensitivity analyses (Allison, 2014; Dziura et al., 2013; Mallinckrodt et al., 2012). All analyses will be implemented in the latest release of SAS/STAT PROC MI in SAS version 9.4 with the inclusion of a new Not Missing at Random option (Demirtas & Schafer, 2003; Little, 2009; Enders, 2010).

Baseline Analyses and Sites. Randomization is expected to produce a high degree of similarity between treatment groups, but treatment groups will be compared at baseline to determine comparability on the outcome variables and to identify potentially important covariates that are not of primary interest in the hypotheses but relate to the outcome criteria. Baseline scores will be used as covariates. Differences between active duty or veteran status and interactions of status by treatment are not expected once relevant patient characteristics such as baseline severity are controlled, but preliminary analyses will consider the need to include site in the analysis designs.

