4. Brief Inventory of Psychosocial Functioning: The Brief Inventory of Psychosocial Functioning (Marx et al. 2013) is a 7-item self-report instrument measuring respondents' level of functioning in seven life domains: romantic relationship, relationship with children, family relationships, friendships and socializing, work, training and education, and activities of daily living. Respondents indicate the degree to which they had trouble in the last 30 days in each area on a 7-point scale ranging from "0 = Not at all" to "6 = Very much."
5. Demographics and Military Service Characteristics Form: The Demographics Form measures standard demographics (race, gender, age) and military service information (e.g., rank).
6. Combat-Related PTSD Beliefs Inventory: The Combat-Related PTSD Beliefs Inventory is being added to Project Remission study as a self-report measure of participant's general beliefs about combat-related PTSD. On each of the four items, participants will be asked to rate the degree to which they agree or disagree with the statements on a 1 to 10 scale with 1 = Strongly Disagree and 10 = Strongly Agree. The measure was created specifically for Project Remission. Therefore, there are no validity or reliability data on the measure. The results of each item will be compared with posttreatment change scores on the PCL-5 and CAPS-5 to determine if they are correlated with treatment response.

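### Correlating Beliefs Inventory items with PCL-5 and CAPS-5 change scores, with no stated baseline adjustment, can mistake baseline severity for a predictor of treatment response

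*Protocol*

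**What the plan says.** Section 16.0, item 6 describes a four-item inventory written for this trial: "On each of the four items, participants will be asked to rate the degree to which they agree or disagree with the statements". Ratings run from 1 to 10. The section adds: "Therefore, there are no validity or reliability data on the measure". The analysis is given in one sentence: "The results of each item will be compared with posttreatment change scores on the PCL-5 and CAPS-5". Its stated purpose is to learn whether the ratings are associated with response to treatment. The schedule in section 7.3 (row "6. Combat-Related PTSD Beliefs Inventory") has the inventory at baseline only, so the items serve as predictors.

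Baseline adjustment is mentioned elsewhere. Section 7.4.3.1, in the paragraph on baseline comparability and sites, says: "Baseline scores will be used as covariates". Section 7.4.3.2 enters the baseline level as a covariate in the mixed models for Hypotheses 1 to 3. Neither place mentions the Beliefs Inventory. Section 7.4.1 also quotes power for bivariate correlations, a method that carries no covariates.

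**The concern.** Change is baseline minus post-treatment, so part of any correlation with change is a correlation with the baseline score itself. Patients who start higher have more room to fall, and chance elevation at entry recedes. A belief item that merely goes along with being more severely ill shares in this, even if it says nothing more about outcome once severity is known.

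The sentence in item 6 names the outcome, the type of association and the conclusion to be drawn, so this is a stated method and not only a detail left for later. At stake is one interpretive claim: that beliefs about combat-related PTSD relate to response. There are 4 items x 2 outcomes = 8 such tests.

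**Working it through.** **Inputs**
- Pre-post correlation r = .50 (section 7.4.1).
- PCL-5 "baseline standard deviation of about 15"; no post-treatment SD is given. Let k = SD post / SD baseline, varied from 1 to 2 (assumption).
- N = 200, from 100 per group in section 7.4.1; 250 are to be randomized (section 7.1.1).
- Correlation of item with baseline severity, q = .1, .2, .3 (assumption; the protocol has no data on it).
- Two-sided alpha .05 (assumption; it reproduces the stated power figures).

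**The plan's own figures**
- Correlation of .30, N = 100: atanh(.30) x √97 = .3095 x 9.849 = 3.05, so power is Φ(3.05 − 1.96) = .86 by Fisher z. The noncentral t gives .876. Stated: .88.
- ANCOVA, stated as r = .50 "between baseline and post-treatment is .81 to detect a standardized mean difference of .35": .35/√(1 − .25) = .404; .404 x √50 = 2.86; Φ(2.86 − 1.96) = .815.

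Both agree with the protocol.

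**Coupling of baseline and change**

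corr(baseline, change) = (1 − rk)/√(1 + k² − 2rk)

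An item related to outcome only through measured baseline has corr(item, change) = q x that value. The chance of p < .05 is Φ(z − 1.96) + Φ(−z − 1.96), with z = atanh(corr) x √(N − 3).

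| k | corr(baseline, change) | corr(item, change), q = .1/.2/.3 | rate at N = 200 |
|---|---|---|---|
| 1 | .50 | .050/.100/.150 | .11/.29/.56 |
| 1.25 | .33 | .033/.065/.098 | .07/.15/.28 |
| 1.5 | .19 | .019/.038/.057 | .06/.08/.13 |
| 2 | 0 | 0/0/0 | .05/.05/.05 |

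Simulation agrees to within about .02; the .28 and .13 came out as high as .30 and .14. With k = 1 the rates are .08/.17/.32 at N = 100 and .12/.35/.66 at N = 250. Above k = 2 the coupling changes sign (−.12 at k = 2.5). With the baseline score as covariate, the simulated rate was .046 to .056 in every case.

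**Measurement error in baseline**

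Suppose the item tracks true severity and the baseline score has reliability λ (assumption). Then corr(item, post) = qr/λ, and:
- unadjusted: corr(item, change) = q(1 − kr/λ)/√(1 + k² − 2rk)
- adjusted: partial corr(item, post given baseline) = qr(1/λ − 1)/√((1 − q²)(1 − r²)), with z = atanh(partial) x √(N − 4)

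For q = .3 and N = 200:
- λ = .9, k = 1: unadjusted .133, rate .47; adjusted .020, rate .06.
- λ = .8, k = 1: unadjusted .113, rate .35; adjusted .045, rate .10.
- λ = .7, k = 1: unadjusted .086, rate .23; adjusted .078, rate .19.
- λ = .5, k = 1: unadjusted 0, rate .05; adjusted .182, rate .73.
- λ = .8, k = 1.5: unadjusted .014, rate .05; adjusted .045, rate .10.

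With equal SDs, adjustment is clearly nearer 5% at reliability .8 to .9. The two analyses are close at .7, and below that the change score does better.

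**The case against.** The case on the other side has five parts.

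1. **Silence is not a specification.** Item 6 is one sentence in the instrument list, and section 7.4.3.1 says in general terms that baseline scores are covariates. Section 7.4.3.2 also speaks of change scores while adjusting for baseline. A reader might infer that the protocol prescribes an unadjusted correlation. It does not; it leaves adjustment unstated. What remains is that the only method named for these items is a correlation with change, and that neither statement about covariates is tied to it.

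2. **The effect is not certain.** A reader might infer that a severity-related item will show up as a predictor. The documents do not support this, because they give neither the item-severity correlation nor the post-treatment SD. A larger post-treatment SD is plausible: entry requires a PTSD diagnosis, which may narrow the baseline range, and outcomes should divide into remitters and non-remitters. In favour of equal SDs, under which change has the baseline SD, the detectable differences in section 7.4.1 fit: .40 x .866 = .346, against the stated .35. That is consistent with equal SDs but does not establish them.

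3. **Adjustment can be the worse analysis.** If much of the gap between r = .50 and 1 is baseline measurement error, adjusting leaves residual confounding. This stands, as the reliability figures show, and it limits the recommendation.

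4. **A correlation that runs through severity is still a correlation with response.** This also stands. The excess rates are misleading only if the result is read as prediction beyond severity, so the question has to be stated.

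5. **Leaving out treatment arm causes no bias.** Correct. The items are collected before randomization, so adding arm is only a gain in precision.

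**Conclusion.** The point holds as a possibility of modest weight. As item 6 stands, an item that carries no information beyond baseline severity can appear related to treatment response. The excess is large if the two SDs are equal and the item correlates .2 to .3 with severity. It is small if that correlation is about .1 or the post-treatment SD is 1.5 times baseline, and absent at twice.

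These figures rest on the protocol's r = .50, an assumed item-severity correlation, an assumed SD ratio and an item that acts only through severity. The inventory is in none of Hypotheses 1 to 3 and is not among the endpoints in section 7.4.2, so no conclusion about IOP-PE against Massed-PE depends on it.

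**What to change.** In section 16.0, item 6, or in the analysis plan, state that the post-treatment CAPS-5 or PCL-5 score is regressed on each item with the corresponding baseline score as covariate, in line with section 7.4.3.2. Treatment arm may be added for precision. Label the analysis exploratory, and say that it asks whether beliefs predict outcome beyond baseline severity. The simple correlation with change may be shown descriptively alongside. Note that the adjusted result depends on a reasonably reliable baseline measure; if that is in doubt, reporting both analyses lets a reader see whether they agree.

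The cost is a sentence of text and a line of code. All the variables are already collected.
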